#### 5.2 Exclusion criteria

- More than one obvious cancer in the same breast as diagnosed by clinical examination, mammography or ultrasonography.
- Bilateral breast cancer at the time of diagnosis.
- Ipsilateral breast had a previous cancer and/or irradiation.
- Patients *known* to have BRCA2 gene mutations, but testing for gene mutations is *not* required
- Lobular cancer or Extensive intraductal Component (EIC =>25% of the tumour is intraductal) on core biopsy or initial pathology (if performed)
- Patients undergoing primary medical treatment (hormones or chemotherapy) as initial treatment with neoadjuvant intent of reducing tumour size should be excluded; those given short duration (up to 4 weeks) systemic therapy can be included.
- Patients presenting with gross nodal disease, considered to be clinically malignant or proven cytologically or by scanning. In general, 4 or more positive nodes or extranodal spread are not suitable for Targit alone and should receive EBRT as well. However, individual centres may decide that anything more than micrometastasis should receive EBRT.
- Patients with any severe concomitant disease that may limit their life expectancy.
- Previous history of malignant disease *does not* preclude entry if the expectation of relapse-free survival at 10 years is 90% or greater.
- Any factor included as exclusion criterion in the local centre's Treatment Policy. This is particularly relevant to patients entered into the post pathology stratum.
- No more than 30 days can have elapsed between last breast cancer surgery (not axillary) and entry into the trial for patients in the post-pathology stratification.

## **5.3 Patient entry to the trial**

Patients will be entered to the trial only after being given full information about the trial including a written information sheet (see examples in Appendix). Each patient should be given time to consider participation and ask questions before giving consent by signing the Patient Consent Form (see example see Appendix). A patient deemed suitable for the trial will only be randomised once informed consent has been freely given.

### **5.3.1 Stratum 1 - Pre Pathology Entry**

Those patients who are planned to have IORT at the time of primary surgery will be randomised in this stratum after giving consent but prior to the planned surgery.

### **5.3.2 Stratum 2 - Post Pathology Entry**

These patients may be informed of the trial prior to surgery but should only be asked to give consent once the wide local excision has been performed and full histological examination of the tumour has shown that the patient is eligible. Re-excision to clear margins may be performed if required, provided no other adverse histopathological features were found. If these patients are randomised to, and indeed receive IORT and it is later found that the re-excision is again involved, then further re-excision should be performed until clear margins are obtained, and the patient given whole breast EBRT as well, without the tumour bed boost.

### **5.3.3 Stratum 3 - Contralateral Entry**

If the patient has a previous contralateral breast cancer, then they will be entered as a separate stratum irrespective of whether IORT is being planned as a single or second procedure. The numbers are expected to be too small to split this stratum further.

### **5.3.4 Patient Consent**

The example Patient Information Leaflets and Consent Forms may be modified to meet local criteria but must be approved by the appropriate ethics committee/IRB.

Included on the generic consent form is the optional opportunity for the patient to make a gift of the tissue blocks of the tumour for possible translational investigations. Any tissue donated in this way should only be used with the approval of the International Steering Committee.

## SECTION 6

### TREATMENTS

#### 6.1 Treatment Policy Statements

Prior to entry of any patients each centre will register with the International Steering Committee and complete a Policy Statement (Appendix 3), which will define the categories of patients to be entered (e.g. patients over 50 years, N0) together with some details of treatment policy (e.g. fractionation and dose of conventional radiotherapy to be used). Any change to practice during the course of the trial must be notified to the Steering Committee in writing, prior to implementation. This is to enable the Steering Committee to audit the patients entered and to confirm that treatment remains true to the core protocol.

Only clinical centres with the Intrabeam® or those who are able to refer patients to such a centre may enter the trial. Centres with newly acquired equipment must consult the TARGIT Trial Operations Centre prior to entering patients into the trial. A confirmation of the quality control of the system set up must be received at the Operations Centre before randomisation can begin. (See also Section 6.4.2)

#### 6.2 Surgery

All patients will have local excision of the primary tumour following appropriate clinical work-up. No special assessments prior to randomisation will be required although mammography and ultrasound are recommended to try to exclude multi-focal disease and to determine as accurately as possible the size of the tumour.

Surgery will be according to usual local practice. Complete macroscopic excision of the tumour is required. The aim of the local excision should be to achieve the widest margin of excision whilst maintaining a good cosmetic outcome (aim for margins of >10mm). The final histological margin should be  $\geq 1$ mm clear of all invasive and in-situ disease.

For superficial tumours an ellipse of overlying skin should be excised. The depth of resection will depend on the position of the tumour within the breast and the size of the breast but in most instances will extend to the pectoral fascia.

In all patients, but especially in those women with impalpable tumours where pre-operative localisation has been performed, the specimen should be well orientated with sutures or clips according to local protocols and x-rayed intra-operatively. The specimen x-ray should be examined in theatre to ensure complete excision of the lesion and to help with the assessment of adequacy of the margins. Further tissue should be taken (and marked) from a margin if the x-ray abnormality extends near the margin.

Either a standard sentinel node biopsy or at least level II axillary node clearance must be performed in all patients. Similar surgical techniques must be employed in all patients regardless of the randomisation. Wound closure must be performed meticulously (air and water-tight) as described and sutures (if non-absorbable), should remain in place for 14 days.

## **6.2.1 Pre Pathology Stratum**

### **6.2.1.1 Patients with positive margins**

If final pathology (Section 6.3 below) shows involved or close margins (evidence of invasive or in situ tumour at, or within 1mm, of an excision margin) re-excision is strongly recommended. In some cases, this may necessitate a mastectomy.

For patients who have already received IORT, such re-excision to clear margins should be followed by external beam radiotherapy excluding the boost.

### **6.2.1.2 Patients with markers of poor prognosis (e.g., lobular cancer and Extensive Intraductal Component (EIC))**

It is recommended that patients found on pathological examination of the operation specimen to have either invasive lobular cancer or extensive intra-duct component (or other adverse criterion such as grade 3 tumour, lymphovascular invasion, node involvement, etc) as defined by the local centre) receive external beam radiotherapy since these patients are at a higher risk of developing recurrence in the ipsilateral breast at a site other than that of the excised primary. For those patients randomised to intra-operative radiation this will be in addition to the treatment they have already received and it is recommended that any boost is omitted. These patients shall remain in the trial. However, most of such patients (e.g., lobular carcinoma) would have not been included in the first instance if a preoperative core biopsy had been performed; we recommend this.

Alternatively, a mastectomy may be performed if it is deemed necessary, based on the final histopathology, multidisciplinary meeting and joint consultation between the patient and the clinician, irrespective of the arm of randomisation. This must be recorded on the patient's trial case report forms (CRF); the patient should remain in the trial and continued to be followed according to the protocol.

## **6.2.2 Post Pathology Stratum**

Patients randomised in this stratum should have the initial surgery performed and the histopathological examination completed preferably with clear margins confirmed before being randomised. If no other adverse pathological features are present, patients with involved margins may be randomised provided that, repeat excision to clear margins is performed prior to radiotherapy (IORT or EBRT). If after delivering IORT it is found that the re-excision margin is also involved, then these patients should received EBRT as well, as repeated positive margins are a poor prognostic factor.

The procedure for delivering the IORT will be the same as that described in Section 6.4.1 below, including the administration of a prophylactic antibiotic just after the induction of anaesthesia. In this group of patients, special care should be taken to ensure the wound closure is meticulous, air- and water-tight and sutures are not removed for at least 2 weeks. If an absorbable suture is used it should be at least 3-0 in thickness, should not be absorbable within 2 weeks (do not use "rapide") and Steristrips should be used and left in situ for 2 weeks.

## **6.2.3 Contralateral Stratum**

Patients should be managed as appropriate in the pre or post pathology stratum.

## 6.3 Pathological Examination

Data from pathological examinations should be recorded on the appropriate data collection forms and all reporting of pathological findings are to be in accordance with the TNM Classification. We recommend that the minimum dataset as defined in the British Association of Surgical Oncologists' guidelines should be recorded.

## 6.4 Radiotherapy

### 6.4.1 Intra-operative radiotherapy

The technique of the operation and the delivery of radiotherapy have been described in a video available from the TARGIT Trial Operations Office.

#### Preparation of the Intrabeam

Intra-operative radiotherapy will either be delivered in the operating theatre immediately after the removal of the tumour or as a subsequent procedure, a short time later.

The procedure has been described in detail The papers presentations and video related to TARGIT are available at [www.targit.org.uk](http://www.targit.org.uk) or [www.dundee.ac.uk/surgery/targit/](http://www.dundee.ac.uk/surgery/targit/) and a video demonstrating the operative technique is at [www.theijs.com/media](http://www.theijs.com/media). A brief description is given below:

All patients should receive a prophylactic dose of antibiotic just before skin incision. The device and the arm of the stand are wrapped in a sterile clear plastic cover (see Fig 1). The individual applicators are sterilised prior to the theatre session. The size of the sphere is determined at surgery by the surgeon and/or the radiation oncologist. An appropriately sized Intrabeam sphere fits comfortably without tension in the surrounding tissue so that the skin and subcutaneous tissues can be gathered with a purse string suture over the sphere. Any other apparatus to assist this apposition may also be used.

It is essential that complete haemostasis is achieved before insertion of the applicator sphere, because even a small ooze of blood can distort the cavity around the sphere and significantly change the target dose. The applicator sphere is inserted into the surgical cavity and a deep surgical purse string suture is inserted in the breast tissues to bring together the target breast tissue so that it applies well to the surface of the Intrabeam applicator sphere and holds it in place during treatment. The skin, but not the breast tissue, should be everted and held away from the delivery device by surgical sutures to prevent direct contact with the sphere. One patient in the pilot series described did develop an area of skin necrosis. It is important to keep the skin at a distance of at least 1cm from the applicator.

If necessary, protective caps (made from tungsten impregnated rubber available from Carl Zeiss) may be fashioned by the surgeon to protect deep or superficial structures. If the deep margin of excision is such that left anterior descending branch of the coronary artery could receive significant radiation dose, then the surface of the applicator sphere should be covered with a protective cap at the chest wall. However, in most patients the normal thickness of the chest wall (muscle and rib cage) would provide adequate shielding and such a protective cap is not required. Sometimes superficial skin flap may require protection with a 0.5cm thick, cut piece of wet gauze piece. Care must be taken however, not to inadvertently shield the areas of tissue that require radiation treatment.

## **IORT Dose Prescription and Delivery**

The surgeon and radiation oncologist should choose the largest possible suitable applicator in order to ensure the highest dose is delivered to the tumour bed tissue. Radiation protection shielding material may also be used, which is sterile and suitable for both internal and external use.

The protocol allows for two dose prescriptions. Each participating site should decide on one method and use this procedure for all patients, for the duration of the trial.

Alternative A: A dose of 20 Gy at the surface of the applicator (in water) is prescribed by the radiation oncologist and delivered to the breast tissue. This takes approximately 30 minutes, depending on the size of the applicator. This prescription should be chosen if the clinic is treating mainly larger tumours (applicators  $\geq 4$  cm).

Alternative B: A dose of 6 Gy at 1 cm (in water) is prescribed by the radiation oncologist and delivered to the breast tissue. This also takes approximately 30 minutes, depending on the size of the applicator. This prescription should be chosen if the clinic is treating mainly smaller tumours (applicators  $\leq 4$  cm). This dose is equivalent to 5 Gy at 1 cm (adipose).

Using prescription A ensures that larger tumours receive a higher dose in the tumour bed ( $> 6$  Gy at 1 cm and beyond). This is the reason why Alternative A is recommended for clinics with predominantly larger tumours.

Previous versions of the TARGIT protocol recommended a dose of 5Gy at 10 mm adipose which is equivalent to 6 Gy at 10 mm in water. With the publication of further research it is now recommended that 20Gy at the applicator surface should be adopted by all new sites. This dose has superior radiobiological advantages as it ensures that tumour beds from larger tumours receive a higher dose than small tumours. Details are given in Appendix.

During the radiation treatment, the anaesthetist, clinician and physicist may remain in the room. To avoid unnecessary exposure we recommend that as many people as possible vacate the operating theatre and those remaining, either wear a lead apron or remain behind a shielded screen.

## **Completion of IORT**

After completion of radiation, the conforming stitches are removed. Strict haemostasis should be obtained following the removal of the Intrabeam device. The skin is sutured meticulously to achieve a water-tight closure and a good cosmetic result. If non-absorbable sutures are used, they should be left in situ for 14 days and if absorbable sutures are used, Steristrips covering the entire wound should be left in place for 14 days.

## **IORT Physics**

Prior to entering any patient into the trial, centres will be expected to submit data for each x-ray source (XRS) probe and applicator set in use. Each centre will be responsible for measuring data for the probe and applicator set, and shall submit the data supplied by the manufacturer for comparison with measured data together with a copy of the letter of acceptance supplied by Carl Zeiss.

In addition, five “pilot” cases (non-randomised patients) will be performed followed by an audit by a member of the International Steering Committee (or an appointed delegate).

## **6.4.2 Conventional radiotherapy**

Planning protocols for the conventional radiotherapy will vary from centre to centre but for each centre a written policy will be required (Appendix 3). All patients randomised to receive conventional radiotherapy within this trial should be treated in accordance with this policy. Dosage should only be applied to the breast; axillary, supra-clavicular and internal mammary nodes should not generally be irradiated by discrete fields. Patients with previously irradiated adjacent fields for example, those with previous contra-lateral breast cancer, will need to have the radiotherapy fields modified according to local policies. Recommended guidelines for treatment are given in Appendix.

## **6.5 Adjuvant Systemic Therapy**

Following completion of IORT patients may be recommended appropriate adjuvant therapy according to local practice or trial protocols. For all trial patients, the sequencing of these other therapies is not governed by this protocol, but careful consideration needs to be given for patients randomised to IORT but needing external beam radiotherapy and adjuvant chemotherapy. The policy for such treatments should be declared in the Policy Statement. It is recommended that even the second procedure IORT should be delivered before beginning chemotherapy.

## **SECTION 7**

### **PATIENT FOLLOW-UP AND RECORDING OF EVENTS**

#### **7.1 Follow-up and notification of recurrence, adverse events and death**

Patients should be followed according to local guidelines and these should be noted on the Policy Statement prior to entry into the trial. However, case report forms will be required for each patient at 6 monthly intervals for the first five years and annually thereafter until at least 10 years.

Wherever possible each patient should be seen within a six week window of the anniversary of the therapeutic surgery (eg at 6 months  $\pm$  6 weeks). At each visit the patient should be offered a physical examination and asked whether she has experienced any adverse events.

We recommend that mammography of the ipsilateral breast occurs annually and of the contralateral breast at least every three years. Any other examination is at the discretion of the local clinician.

#### **7.2 Recording of recurrence/new malignancies**

Recurrence includes any new occurrence of breast cancer apart from new disease in the opposite breast in the absence of previous recurrence (which is classified as a contralateral breast cancer). Local recurrence, for the purposes of this protocol, is defined as recurrence in the index quadrant of the breast. Loco-regional recurrence is defined as recurrence either in the ipsilateral breast (other than the index quadrant) or in the axilla. Ipsilateral supraclavicular and intramammary node recurrence are not classified as local recurrence since the prognosis of patients with recurrence at these sites is more similar to distant than loco-regional disease.

Confirmation of ipsilateral recurrence must be by histology or unequivocal cytology. Clinical examination and imaging are not sufficient. Careful recording of the site of the recurrence is required to determine whether it is at the site of the original tumour and/or within the treatment field to determine whether the disease is 'local' or 'loco-regional'.

Recurrence at any other site must be confirmed by appropriate imaging and/or biopsy. Details of both first loco-regional (breast and axilla) and first distant recurrence are required as well as the status of the patient with regard to active disease when treatment for local disease has been completed.

Development of new malignancy (including the contralateral breast) must be reported on the case report forms once a diagnosis has been confirmed.

#### **7.3 Guidelines for the Management of Recurrence**

The management of recurrent disease will be left to the discretion of the participating institution/investigator. If appropriate, patients having had IORT alone are able to have conventional irradiation as part of the management of a recurrence. It may also be possible for patients who have received external beam treatment to have IORT after surgical excision of the recurrence, particularly if they wish to avoid mastectomy.

## 7.4 Adverse Events

This section describes the minimum reporting procedures for the trial, based on current UK and European Union legislation. Local and national policies may require additional reporting of safety data, including adverse events.

The International Steering Committee and the DMC will review data on adverse events and complications. If a local or national policy requires a summary of this review (e.g. for an annual report), please contact the TARGIT Trial Operations Office.

Acute and late radiation morbidity must be graded according to the RTOG criteria and ‘pain due to radiation’ according to the Common Toxicity Criteria. These are the only expected adverse events and must also be recorded on the Complications Form. Adverse events may be recorded at any time following the surgery and a new form should be completed for each episode.

### 7.4.1 Serious Adverse Events

A Serious adverse events (SAE) is defined as any event that is fatal; life threatening; causes or prolongs hospitalisation; causes disability or incapacity or requires medical intervention to prevent permanent impairment or damage, any grade 4 toxicity.

### 7.4.2 Adverse Events Reporting Requirements

Immediate reporting of any SAE must be made either directly to the International TARGIT Trial Operations Office or via the local randomisation centre as soon as possible and at least within 5 working days of the investigator becoming aware of the occurrence of the event. SAEs must be reported whether or not considered related to the treatment under investigation. An early report can be followed up by a more detailed report.

All serious adverse events that occur during the period of observation (see next section) must be documented on the ‘Serious Adverse Event Form’. It is also the investigators’ responsibility to report them to the local institutional ethics committee as required by local regulations.

- For all serious adverse events, the following must be assessed and recorded on the SAE reporting form: intensity/severity; relationship to treatment; action taken; outcome to date.
- Adverse events must also be recorded in the subject’s medical records.

The clinical course of the serious adverse event should be managed according to accepted standards of medical practice until a satisfactory explanation is found or the investigator considers it medically justified to terminate follow-up of this event. Should the adverse event result in death, a full pathologist’s report should be supplied, if possible. Any complications following surgery ( $\pm$  intra-operative radiotherapy) must be reported on the Complication Form.

### 7.4.3 Period of Observation

For the purpose of this trial the period of serious adverse event (SAE) observation extends from the time of registration onto the trial until 90 days after the completion of randomised treatment. Trial follow-up should continue according to schedule once the SAE is resolved.

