### OBJECTIVES

This is a pragmatic trial that compares two treatment policies in patients with early breast cancer who have undergone local excision of a good prognosis tumour. The conventional policy is that each patient receives a radical course of external beam radiotherapy (with or without a boost) according to local treatment guidelines. The experimental policy is to give targeted intra-operative radiotherapy in a single dose recognising that some patients randomised to this treatment, because of unfavourable features found subsequently in the pathological examination of the excised lesion, will need to have external beam therapy in addition (without the boost which has been provided by the targeted dose). This could happen in 10 to 15% of cases. A nested study allows randomisation of patients to IORT or EBRT after the pathological examination of the removed lesion. Patients in this randomisation who are allocated IORT will require a second surgical procedure for administration of the radiation.

The objective of the trial, regardless of the exact procedure followed, is to provide local tumour control but the two treatments involve very different time and financial commitments on behalf of the individual patient and the health service.

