### 9.3 Early Stopping

The DMC would keep under review the full range of adverse event data being collected and draw conclusions on safety by considering all events. If however any of the following were demonstrated at  $p < 0.01$  they would consider recommending early stopping:

- A significant increase in grade 4 skin or rib fractures (as a sign of radionecrosis)
- Delays in wound healing which after detailed review by the DMC as to time course and severity were considered clinically significant.

Early stopping could be applied on specific strata, while other strata are allowed to continue recruitment.

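### The SAE window in protocol 7.4.3 is tied to the end of treatment, so it is generally longer under EBRT than under IORT alone, and its end is undefined for IORT patients who also have EBRT

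*Combined protocol and SAP*

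**What the plan says.** Protocol 7.4.3 sets the period of SAE observation. It "extends from the time of registration onto the trial" and lasts "until 90 days after the completion of randomised treatment". The rule is worded identically for both arms.

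The two randomised treatments end at different times:

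- **IORT.** Protocol Section 2 (Objectives) states: "The experimental policy is to give targeted intra-operative radiotherapy in a single dose". Protocol 6.4.1 has it given "immediately after the removal of the tumour or as a subsequent procedure, a short time later".
- **EBRT.** Protocol 6.4.2 says: "Planning protocols for the conventional radiotherapy will vary from centre to centre". On adjuvant systemic treatment, protocol 6.5 adds that "the sequencing of these other therapies is not governed by this protocol".
- **Both.** Protocol Section 2 expects 10 to 15% of patients allocated IORT to need EBRT as well.

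Causality does not narrow what is reported. Protocol 7.4.2 says: "SAEs must be reported whether or not considered related to the treatment under investigation". Under protocol 9.3 the DMC is to "draw conclusions on safety by considering all events". SAP 7.2 lists local toxicity and morbidity as a secondary comparison between arms. SAP Section 10 refers to earlier descriptions for toxicity and names no observation window for it.

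**The concern.** The window closes on a date that depends on the allocated arm. Both arms get 90 days after their own treatment, but the time from registration to that point includes the wait for EBRT and the EBRT course in one arm and neither in the other. Because unrelated SAEs count, any extra time adds events. Chemotherapy given before EBRT would fall inside the EBRT window, while the same chemotherapy after IORT alone could fall largely outside the IORT window.

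A raw count of SAEs, or the percentage of patients with at least one, would then tend to be higher under EBRT even if the treatments were equally safe.

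The second gap is the IORT patient who goes on to EBRT. The protocol does not say whether her randomised treatment ends at the IORT dose or at the last EBRT fraction. If it ends at IORT, SAEs during EBRT, which is part of the policy under test, may go unrecorded on the SAE Form. SAP Section 10 also plans toxicity by treatment received (TARGIT only, both, EBRT only). Any SAE data used there would come from three groups with different or undefined windows.

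**Working it through.** The plan states no window length or ratio, so there is no figure to reproduce. The ratio needs inputs that the available text does not give, so it is shown as a range.

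**From the documents:** 90 days after treatment in both arms (7.4.3); IORT course length 0 days (Section 2); 10 to 15% of the IORT arm also having EBRT (Section 2).

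**Assumed, not in the documents (days):**

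- Registration to surgery, pre-pathology: *a* = 0 to 28
- EBRT course: *c* = 21 to 45
- Surgery to EBRT start, pre-pathology: *w* = 28 to 84 without chemotherapy, 126 to 196 if chemotherapy comes first
- Post-pathology, counted from registration: IORT at *i* = 7 to 28, EBRT start at *w* = 14 to 42 without chemotherapy

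Registration and randomisation are taken as the same day.

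**Step 1: window ratio, EBRT to IORT alone.**

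Pre-pathology: R = (a + w + c + 90) / (a + 90). Post-pathology: R = (w + c + 90) / (i + 90).

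| Setting | Lowest | Highest |
|---|---|---|
| Post-pathology, no chemotherapy | (14+21+90)/(28+90) = 125/118 = 1.06 | (42+45+90)/(7+90) = 177/97 = 1.82 |
| Pre-pathology, no chemotherapy | (28+28+21+90)/(28+90) = 167/118 = 1.42 | (0+84+45+90)/90 = 219/90 = 2.43 |
| Pre-pathology, chemotherapy first | (28+126+21+90)/(28+90) = 265/118 = 2.25 | (0+196+45+90)/90 = 331/90 = 3.68 |

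R exceeds 1 whenever EBRT would end later than the day on which IORT would be given. That holds in every case tried.

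**Step 2: dilution by IORT patients who also have EBRT.** Suppose their window is read as running to the end of EBRT. With a fraction *f* of such patients, the IORT arm's mean window is (1−f) × (IORT window) + f × (EBRT window). For *a* = 0 to 14 and *f* = 0.10 to 0.15, pre-pathology:

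- No chemotherapy, lowest: 153 / (0.85×104 + 0.15×153) = 153/111.35 = 1.37
- No chemotherapy, highest: 219 / (0.90×90 + 0.10×219) = 219/102.9 = 2.13
- Chemotherapy first, by the same formula: 251/126.05 = 1.99 to 331/114.1 = 2.90

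If their window is read as ending at IORT, the Step 1 ratios apply. The undefined end date therefore changes the answer.

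**Step 3: from window to counts, with no true difference.** Let *s* be the share of IORT-window SAEs that are peri-operative and seen in both arms, with the rest arising at a constant rate. The count ratio is C = s + (1−s)R and the person-time rate ratio is C/R. For R = 1.7:

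| s | Count ratio | Rate ratio |
|---|---|---|
| 0 | 1.70 | 1.00 |
| 0.5 | 0.5 + 0.5×1.7 = 1.35 | 0.79 |
| 0.9 | 0.9 + 0.1×1.7 = 1.07 | 0.63 |

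The window ratio equals the count ratio only when the SAE rate is constant. With early clustering, dividing by person-time does not restore 1; it moves the comparison the other way.

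**The case against.** The strongest reply is that 7.4.3 limits only the SAE Form, and most safety information lies elsewhere. Protocol 7.4 lets adverse events be recorded at any time after surgery. Protocol 7.1 requires CRFs six-monthly for five years and then annually to at least ten, in both arms, and asks about adverse events at each visit. Protocol 7.5 requires every death to be reported. Protocol Section 4 includes late skin reactions among the toxicities. The DMC reviews all the adverse event data collected, and its named triggers in 9.3 concern skin and rib events and wound healing, not total SAEs. No passage specifies a between-arm analysis of SAE counts. Protocol 7.4 also presents its rules as minimum reporting requirements based on legislation, and equal follow-up after each arm's own treatment is a sensible reporting rule.

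All of that stands, and it confines the point to SAE Form data. It does not remove it. The Complications Form is described for radiation morbidity, radiation pain and surgical complications, so unrelated or chemotherapy-related SAEs have no clearly equivalent record. Nothing in the SAP prevents SAE Form counts from being set side by side by arm.

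A reader might infer that EBRT patients are watched for a known multiple of the IORT time, for example 1.7 to 3.4, and that the safety comparison as a whole is biased towards IORT. The documents support neither. Counted from surgery, 1.7 needs 63 days to the end of EBRT (0.7×90) and 3.4 needs 216 days (2.4×90); neither interval is stated. Nor is 1.7 a floor. The direction depends on the measure, as the person-time figures show.

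**Conclusion.** The point holds for the SAE Form. Its window is tied to treatment, is generally longer under EBRT than under IORT alone, and has no defined end for IORT patients who also have EBRT. Raw counts, or the percentage with any SAE, would tend to be higher under EBRT without a true difference.

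The mechanism follows from the text; the size does not. Under the assumed timings the window ratio runs from 1.06 to 3.68, with the upper part requiring chemotherapy before EBRT. The effect on counts is smaller if SAEs cluster around surgery. It could be larger if chemotherapy adds SAEs in the extra time, but the documents give no SAE rates with which to judge this. Complications Form toxicity, deaths and routine CRF data are not limited by this window.

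**What to change.** **Protocol 7.4.3.** End SAE observation at one fixed time from randomisation in both arms, long enough to cover planned EBRT, for example 12 months. The longest EBRT window in the assumed range is 28+196+45+90 = 359 days, so 12 months would cover it. Allow no treatment-dependent extension, because that would bring back an arm-dependent end. The window ratio is then 1.0 by construction. The cost is some months more SAE reporting for IORT patients.

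**SAP Section 10, toxicity line.** All 3451 patients are already randomised, so a protocol edit cannot recover SAEs that were never collected. For existing data, state that:

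1. arms are compared over common windows from randomisation (for example 0 to 12 months, then to 5 years), using the Complications Form and the six-monthly CRFs;
2. SAE Form counts from the treatment-anchored window are not compared between arms, and are only described together with observation time by arm;
3. a named date counts as the end of randomised treatment for IORT patients who also had EBRT.

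This costs a few sentences and no new data collection. Its limit is that all-cause SAEs falling outside the old window cannot be rebuilt from these forms with any assurance.
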